**Fig. 3 Fig3:**
[figure not shown]
Flow chart of the LEAD project. GP: General Practitioner

With their patients’ consent, the GPs will be posted a letter inviting them to complete a review of the patient’s medical records at the general practice and to take part in an interview. The letter will be posted together with a GP review proforma, the patient’s consent form, and a reply-paid envelope. A reminder letter will be sent 2 weeks after the initial invitation. To increase GPs’ interest in taking part in the study, a certificate of participation will be provided to GPs who complete the review. The GPs will be able to use this certificate to self-report to relevant medical colleges for Continuing Professional Development points. As an incentive to take part in the interview, the GPs will be offered a $200 gift card, In line with the average hourly consultancy rate for a GP and for lost earnings during the interview.

#### Hospital specialists

Hospital specialists at the five study sites providing care to lung cancer patients will be invited to take part in a qualitative interview. Hospital specialists will include thoracic surgeons, respiratory physicians, medical oncologists, radiation oncologists, nurses, radiologists, pathologists, palliative care physicians, social workers, and allied health professionals. The LEAD coordinators at each site will send an invitation email to these staff and ask interested staff to contact the project manager directly. A reminder email will be sent 2 weeks after the initial invitation. No financial incentive payment will be provided to the specialists as the interviews will be conducted during their normal working hours at the study sites.

### Data collection and measures

#### Patient Survey

The patient survey comprises the Cancer Symptom Interval Measure (C-SIM) used in previous lung cancer studies [19, 20]. It includes questions on the timing of the onset and presentation of symptoms potentially related to lung cancer, as well as questions about GP-initiated tests and the patient’s socio-demographic characteristics (e.g. education, occupation), health status (e.g. smoking history and co-morbidities), and health literacy. When completing the survey, the patients will be able to choose: 1) to complete the survey anonymously, or (2) to provide identifiable personal information and written consent for the research team to access their hospital and general practice medical records.

#### GP review proforma

GP review proforma is based on an earlier one used by J Emery, F Walter, V Gray, C Sinclair, D Howting, M Bulsara, C Bulsara, A Webster, K Auret, C Saunders, et al. [20]. It captures key data on presentations to general practice and investigations conducted by GPs prior to referring the patient to a specialist. It will also collect demographic and health system information of the GP’s practice.

#### Case-note analysis tool

Data for the case-note analysis will be collected using an audit tool with identifiable patient information removed. This audit tool is based on those previously used by the research team [21, 22] and will collect data relevant to lung cancer diagnosis and treatment (e.g. date of diagnosis, date of GP referral) and patients’ demographic background (e.g. gender, age).

#### Qualitative interviews

Questions for the interviews with lung cancer patients, GPs, and hospital specialists will be developed from the Model of Pathways to Treatment, and cover patient, health provider, and health system factors that might influence the diagnostic pathway of lung cancer patients. For interviews with lung cancer patients, questions will also be based on the interview schedule used in an earlier study [20]. With participants’ consent, all interviews will be audio-taped.

Lung cancer patients will be able to choose to have the interview conducted face-to-face or via telephone. The interview will be conducted at a time convenient to the participant and will last approximately 1 hour. For CALD patients, a qualified interpreter or a bilingual researcher will be involved in the interview as required. The patient’s carer is welcome to take part in the interview if preferred by the patient. For GPs and hospital specialists, the interviews will be conducted via telephone at a time convenient to the participant. The interview will last between 30 min to 1 hour.

### Ethics, consent and permissions

Our project has received ethics approval for a multiple-site study from the Monash Health Human Research Ethics Committee (HREC/16/MonH/311) and research governance approval from all participating sites. Three forms of consent will be used in the study: waiver of consent, implied consent and written consent. Waiver of consent will be used for the case-note analysis component and implied consent will be used for the patient survey and the GP review components. Written consent will be obtained for patients who have provided consent in the survey for the research team to access their hospital and general practice medical records. It will also be used for all participants in the qualitative arm.

### Statistical Considerations

#### Quantitative component

Comparions between CALD and Anglo-Australian patients on time intervals will be performed using the logrank test. Cox proportional hazards regression will be used to estimate the relative effect of factors (e.g. patient factors, healthcare provider factors, health systems factors) on the underlying hazard rate governing time intervals. Independent groups will be compared using t-tests for continuous variables and chi-square tests for categorical variables. Linear modelling methods for continuous and categorical data may also be used to undertake comparisons adjusted for selected covariates.

A Danish cohort study demonstrated that 60 days was a clinically significant diagnostic interval beyond which mortality increased [23] while another study reported that the median tumour volume doubling time of all lung cancers is 98 days (IQR 108 days) [24]. Based on these data, a 20% increase in tumour size every 28 days appears plausible and capable of affecting disease staging. A between-group difference in the time to treatment of 28 days or more would therefore be clinically significant. A total of 290 participants (145 per group) will provide 90% power with a two-sided alpha of 0.05 to detect an absolute difference of 28 days in median time to diagnosis (60 days versus 88) based on a log-rank test. We anticipate that 724 patients (362 per group) will need to be contacted in order to obtain a sample of this size assuming a 50% patient survey completion rate (based on previous studies, e.g., Emery et al., 2013; Walter et al., 2015), and a 80% GP review completion rate.

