### Lung cancer among the CALD population

The LEAD project focuses on these differences, because there is evidence suggesting that compared to Caucasian lung cancer patients, CALD patients are a vulnerable group, with poorer survival rates and a lower likelihood of receiving timely and appropriate treatment [9–12]. Possible reasons for these poorer outcomes include more advanced stage at diagnosis, cultural beliefs towards treatment, fatalism and medical mistrust [10, 13, 14].

Similar to many Western countries, people from CALD backgrounds account for a significant proportion of Australia’s population. Data from the most recent census shows that in 2016, Australia’s population consisted of people from over 300 ethnic groups with more than a quarter (26%) born overseas and a further one-fifth (20%) having at least one overseas-born parent [15]. This cultural diversity has been reflected in lung cancer patients. A recent retrospective cohort study with six public and two private hospitals in Victoria Australia found that, of the 1417 patients diagnosed with lung cancer between 2011 and 2014, 51% were born overseas [16].

However, most of current research with the CALD population has been conducted in the United States (US). Given the significant differences in the healthcare system and the composition of the CALD communities between Australia and the US (for example, the top three countries of birth for the overseas-born population in 2016 were England, New Zealand, and China for Australia [Australian Bureau of Statistics, 2017], and Mexico, China and India for the US [Migration Policy Institute, 2018]), it is important to explore whether the finding of poorer outcomes among CALD lung cancer patients in the US studies also applies to the Australian context.

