### Model of Pathways to Treatment

The diagnostic and treatment pathway of lung cancer patients is complex, comprising multiple stages from patients noticing symptoms and seeking help from health professionals, to obtaining a formal diagnosis and starting treatment [6]. It is, therefore, useful to apply a theoretical model in cancer pathway studies to inform the description and measurement of the stages along this pathway [6].

The Model of Pathways to Treatment [8] will be used in the LEAD project as the theoretical model to understand and measure the cancer diagnostic and pre-treatment pathway. This model is built on the findings from a systematic review and has been incorporated into the Aarhus Statement, an international guideline for the design and reporting of studies on early cancer diagnosis [6]. An important feature of this model is that it uses events that can be readily understood by patients, clinicians and researchers to define the key time intervals underlying this pathway [8]. As shown in Fig. 1, these intervals are: (1) the appraisal interval (time between first detection or awareness of a symptom to recognising a need to discuss the symptom with a healthcare professional), (2) the help-seeking interval (time from recognising the need to discuss their symptoms to attending the first consultation with a healthcare professional); (3) the diagnostic interval (time from first consultation to a formal cancer diagnosis), and (4) the pre-treatment interval (time from the formal diagnosis to initiation of treatment) [8].

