### Study aims

The two aims of the LEAD project are (1) to explore the differences in the four time intervals along the lung cancer diagnostic pathway between CALD and Anglo-Australian patients, and (2) to explore patient, health care provider, and health system factors that are associated with the differences in time intervals between the two groups. Based on earlier studies, we hypothesise that CALD patients will report longer time intervals than Anglo-Australian patients. There is no specific hypothesis associated with the second research aim because it is exploratory in nature.

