#### Lung cancer patients

Lung cancer patients will be involved in both the quantitative and the qualitative components of LEAD. The quantitative component involves a patient survey and a case-note analysis of hospital records. The qualitative component involves an interview. The patient eligibility criteria are: (1) have a diagnosis of primary lung cancer at the study sites within the past month or during the recruitment phase, and (2) be of CALD or Anglo-Australian descent. We will use prospective recruitment and also include patients who have been diagnosed within the past month to minimise the risk of recall bias and participant attrition due to death or terminal illness.

Patients of CALD descent are defined in the study as those who were born overseas and from one of the following ethnic groups: Arabic, Chinese, Greek, Italian, and Vietnamese. These are the most common ethnic groups for overseas-born people in Australia [15]. Anglo-Australian patients will be defined as those who were born in Australia or other major English-speaking countries (Canada, New Zealand, the United Kingdom, and the US). Patients who are pregnant or aged under 18 years will be excluded from the study because lung cancer among these two groups is very uncommon and those patients tend to have a different diagnostic pathway to the general population [17, 18].

Eligible patients will be identified through the list of new cases presented at the respective lung multidisciplinary team meetings. Additional recruitment sources, such as the bronchoscopy lists, might be used for some study sites on a local basis. The project coordinators will regularly go through these lists throughout the recruitment phase or until the required sample size has been reached.

After an eligible patient has been identified, the site coordinator will send a letter to invite the patient to participate in the patient survey and the patient interview. Patients may consent to take part in either or both activities. A waiver of consent has been obtained for the case-note analysis of hospital records, and the required data will be gathered by a hospital staff member with authorised access to medical records.

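### For the pre-treatment interval, the planned log-rank/Cox comparison on its own cannot separate whether treatment starts from how soon it starts

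*Protocol article*

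**What the plan says.** The protocol article, Statistical Considerations, Quantitative component, gives one method for group differences: "Comparions between CALD and Anglo-Australian patients on time intervals will be performed using the logrank test". For explanatory factors, "Cox proportional hazards regression will be used to estimate the relative effect of factors". Neither sentence excepts an interval. The first aim (Study aims) is "to explore the differences in the four time intervals along the lung cancer diagnostic pathway between CALD and Anglo-Australian patients", and the fourth of these (Model of Pathways to Treatment) is "the pre-treatment interval (time from the formal diagnosis to initiation of treatment".

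Eligibility (Lung cancer patients) requires a diagnosis of primary lung cancer. It does not require that treatment starts. The Background reports "poorer survival rates and a lower likelihood of receiving timely and appropriate treatment" among CALD patients in the cited literature. Recruitment close to diagnosis is chosen partly to "minimise the risk of recall bias and participant attrition due to death or terminal illness". The Background also says that at least half of lung cancer patients in a six-country analysis were diagnosed late, when cure is unlikely.

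The article gives no share of patients who never start treatment and does not say how such a patient enters the comparison. The sample size rests on median time to diagnosis (60 against 88 days), although the 28-day clinical threshold is worded as time to treatment.

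**The concern.** Every enrolled patient has been diagnosed, so every diagnostic interval has an end date. The pre-treatment interval is different: death before treatment, or no treatment at all, leaves it open. That some patients fall into this class is an inference, since the article never says so, but late-stage diagnosis and expected deaths make it a sound one.

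For such an interval the groups can differ in two ways: in the share who ever start, and in the speed of starting among those who do. One hazard ratio or log-rank p-value combines the two, in a mix that depends on how untreated patients are handled. Excluding them conditions on a future event and removes any difference in uptake. Censoring them early largely removes it. Keeping them at risk turns lower uptake into what looks like delay, and dilutes a real delay when uptake is equal. At stake is what the study can conclude about one of its four intervals.

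**Working it through.** **Step 1. The plan's own figure.** Inputs from the Quantitative component section: medians 60 and 88 days, two-sided alpha 0.05, power 90%, equal groups. Assuming exponential times, HR = 60/88 = 0.682.

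- Schoenfeld events: 4 × (1.960 + 1.282)² / (ln 0.682)² = 42.03 / 0.1467 = 287 (rounded up).
- Freedman events: (1.682/0.318)² × 10.51 = 294.
- Power with 290 events: 90.3%.
- Patients to contact: 290 / (0.5 × 0.8) = 725, against 724 stated.

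The stated 290 reproduces, with every patient counted as an event. That fits time to diagnosis, which all eligible patients reach.

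**Step 2. Handling of untreated patients.** Assumed inputs, none of them in the documents: exponential waits among the treated, a 365-day window, median 120 days to death in never-treated patients, and median 20 days to a recorded decision not to treat. From the documents: 145 per group. With 4,000 simulated studies per scenario, the Monte Carlo standard error is at most √(0.25/4000) = 0.8 percentage points. Cells show the hazard ratio for starting treatment (CALD relative to Anglo-Australian, one-step estimate) and the log-rank rejection rate.

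| | Never treated, Anglo / CALD | Median wait if treated (days) | Excluded | Censored at decision | Censored at death | Kept at risk to day 365 |
|---|---|---|---|---|---|---|
| A | 20% / 20% | 30 / 30 | 1.00, 4.5% | 1.00, 5.0% | 1.00, 5.0% | 1.00, 5.4% |
| B | 10% / 25% | 30 / 30 | 1.00, 5.1% | 0.88, 16.1% | 0.72, 72.1% | 0.68, 84.8% |
| C | 20% / 20% | 30 / 44 | 0.67, 82.6% | 0.69, 75.5% | 0.81, 34.3% | 0.85, 22.3% |
| D | 20% / 35% | 30 / 22 | 1.39, 60.4% | 1.09, 9.2% | 0.81, 34.5% | 0.76, 49.2% |

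The last column corresponds to a Gray-type comparison, because the only other censoring is at the end of the window.

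- A: no difference of either kind, and every rule holds the 5% level.
- B: uptake differs, timing does not. The signal is absent under exclusion and strong when untreated patients stay at risk.
- C: real delay, equal uptake (30/44 = 0.682, the design ratio). The pattern is the other way round.
- D: lower uptake but faster starts. The direction reverses.

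**Step 3. What cumulative incidence adds.** With untreated share p and median wait m, the proportion started by day t is (1 − p)(1 − 2^(−t/m)).

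| | Day 90, Anglo | Day 90, CALD | Day 365, Anglo | Day 365, CALD |
|---|---|---|---|---|
| B | 0.90 × 0.875 = 0.788 | 0.75 × 0.875 = 0.656 | 0.900 | 0.750 |
| C | 0.80 × 0.875 = 0.700 | 0.80 × (1 − 2^(−90/44)) = 0.606 | 0.800 | 0.80 × (1 − 2^(−365/44)) = 0.797 |
| D | 0.80 × 0.875 = 0.700 | 0.65 × (1 − 2^(−90/22)) = 0.612 | 0.800 | 0.650 |

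C and D look the same at day 90 (70% against 61%) and separate at the plateau. The curve distinguishes delay from lower uptake; a single early time point does not.

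**Step 4. Sensitivity.** With 20% against 30% untreated and equal 30-day waits, rejection is about 5% with treated patients only and about 44% with untreated patients kept at risk. Censoring at death gives 16%, 28%, 38% and 41% for median death times of 30, 60, 120 and 240 days. With 10% against 15% untreated and 120 days, it is 16% censored at death against 20% kept at risk. The ordering holds; the gap depends heavily on the assumptions.

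**The case against.** The strongest reply is that the article prescribes none of the harmful rules. It names log-rank and Cox and says nothing about dropping or censoring untreated patients, and such rules are commonly left to the full protocol or analysis plan. That stands: the silence is not an error. What remains is the method the article does fix, one hazard comparison for every interval, which does not report how many patients start treatment.

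Second, log-rank and Cox are not invalid here. With deaths censored they give a proper cause-specific comparison, and with untreated patients kept at risk the ordinary log-rank test picks up the uptake difference (scenario B). That stands too. A reader might infer that the planned test is wrong and should be replaced; neither the documents nor the figures support that.

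Third, Gray's test has a price. In scenario C it rejects 22%, against 34% with censoring at death (47% if the median death time is 60 days) and 83% in treated patients only. Since the stated hypothesis is longer intervals, making it the main comparison would be a poor trade. This limits the fix.

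Fourth, a reader might take the Background to say that CALD patients more often go untreated, or that unequal access is what the study is about. The phrase is "a lower likelihood of receiving timely and appropriate treatment", mostly from research in the United States, whose relevance to Australia the article itself questions. The aims concern time intervals and associated factors. Likewise "participant attrition due to death or terminal illness" explains the timing of recruitment and gives no untreated rate.

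Finally, the planned chi-square tests could compare treated with untreated patients. They could, but the article does not tie them to this question, and they would not show timing.

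**Conclusion.** The point holds for one interval and as a matter of interpretation. Log-rank/Cox alone on diagnosis-to-treatment cannot tell whether a group difference, or its absence, reflects uptake, speed or both. Under the assumed inputs the rejection rate for one and the same uptake difference runs from 5% to 85% (scenario B), and the hazard ratio goes from 1.39 to 0.76 (scenario D), purely by handling rule. These sizes rest on assumed untreated shares, exponential waits and assumed death and decision times. If nearly all patients start treatment, the problem is small.

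A reader might also infer that 290 is too few. It is not affected: it is derived from time to diagnosis, which every eligible patient completes, and the article makes no power claim for the pre-treatment interval. The diagnostic-interval analysis stands as planned.

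**What to change.** For the pre-treatment interval only:

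1. Keep log-rank and Cox. Include all diagnosed patients, not only those treated, and describe the result as a cause-specific comparison.
2. Report beside it the cumulative incidence of starting treatment by group, over a fixed window from diagnosis. Treat death before treatment and recorded non-treatment as competing events. Show the whole curve, with a window long enough to reach its plateau.
3. Use Gray's test as a supporting comparison only, given its loss of power for pure delay.
4. Do not present Kaplan–Meier medians that censor deaths as actual waiting times. The article does not propose this; the sentence is a safeguard.

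The cost is a few lines of analysis wording, one more estimate to explain, and a check that the case-note audit tool records the date of death and whether the patient was treated (with the date of a decision not to treat, where recorded). The tool already collects diagnosis and treatment data, so new fields may not be needed. Sample size and recruitment do not change.

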#### Qualitative component

Based on our experience, data saturation is likely to be reached with the following interview sample sizes: 60 lung cancer patients (10 patients per language group), 20 GPs, and 20 specialists.

All interviews will be audio-taped, and transcription, translation, coding, and analysis will occur concurrently with data collection. Thematic analysis will be conducted using a constant comparative method to identify similarities and differences in the content [25]. Data will be analysed inductively and deductively. The interviews will then be incorporated into NVivo version 10 for more structured coding and analysis.

## Discussion

The LEAD project is the first Australian study to compare the time intervals along the lung cancer diagnostic pathway between CALD and Anglo-Australian patients. The project will also explore the underlying patient, healthcare provider, and health system factors that influence the time intervals in the two groups. This information will improve our understanding of the effect of cultural diversity on health outcomes among lung cancer patients and will inform future interventions aimed at early diagnosis and treatment for lung cancer, particularly patients from CALD backgrounds.

There are a number of strengths in the design of the LEAD study that could be considered in future studies. Firstly, the Model of Pathways to Treatment (Walter et al., 2012) will be used to conceptualise and measure the various stages along the cancer diagnostic pathway. This model provides clear definitions and measurements of time intervals along the cancer diagnostic pathway and has been incorporated into the Aarhus Statement, an international guideline for the design and reporting of studies on early cancer diagnosis [6]. The adoption of such a model enables a systematic approach in data collection and allows data comparison between studies and across cancer types.

Secondly, the study will use both quantitative and qualitative methods and will collect information from multiple groups, including lung cancer patients, GPs and specialists. The inclusion of these different methods and participant groups is particularly important given the complexity of the cancer diagnostic and pre-treatment pathway. Compared to earlier studies where a single research method or participant group was used [e.g. 10, 13], such an approach enables a more comprehensive picture of the diagnostic pathway.

Thirdly, the study includes both CALD and Anglo-Australian patients. As noted in a systematic review of cancer beliefs in CALD populations, one limitation of current studies in this area is that few have comparator groups of the local population, making it difficult to disentangle local- versus ethnicity-specific factors in these studies [14]. Compared to these studies, the inclusion of both groups in our study enables a direct comparison between the two groups, leading to a deeper understanding of cultural differences in the diagnostic pathways.

In conclusion, the LEAD project will be the first Australian study to provide comprehensive data on the lung cancer diagnostic pathway for CALD and Anglo-Australian patients. Guided by the Model of Pathways to Treatment, this mixed-method, observational cohort study will inform the development of interventions aimed at improving the diagnosis and treatment of lung cancer in multicultural countries.

